## Abstract

**Background:**

Practitioners frequently use informed consent forms to support the physician-patient communication and the informed consent process. Informed consent for surgery often focuses on risk centered information due to high liability risks for treatment errors. This may affect patients’ anxiety of adverse events and the nocebo effect. This study focuses on the optimization of pre-surgical information on risks and complications, and at the same time reconciles these information with legal requirements.

**Methods:**

The development, piloting, and evaluation of evidence-based informed consent forms for total knee arthroplasty (TKA) and related anesthesia procedures will follow the UK MRC Framework for developing and evaluating complex interventions. Conducting different sub-studies, we will (I) qualitatively explore the information acquisition and decision-making processes, (II) develop and pilot test evidence-based informed consent forms on the example of TKA and related anesthesia procedures, (III) conduct a monocentric interrupted time series (ITS) pilot study to evaluate the effects of evidence-based informed consent forms in comparison with standard consent forms, and (IV) perform a process evaluation to identify barriers and facilitators to the implementation of the intervention and to analyze mechanisms of impact.

**Discussion:**

The evidence-based and understandable presentation of risks in informed consent forms aims at avoiding distorted risk depiction and strengthening the patients’ competencies to correctly assess the risks of undergoing surgery. This might reduce negative expectations and anxiety of adverse events, which in turn might reduce the nocebo effect. At the same time, the practitioners’ acceptance of evidence-based informed consent forms meeting legal requirements could be increased.

**Trial registration:**

ClinicalTrials.gov, NCT04669483. Registered 15 December 2020.

German Clinical Trials Registry, DRKS00022571. Registered 15 December 2020

## Introduction

### Background and rationale

In most countries, every medical intervention requires informed consent [1–4]. Appropriate informed consent procedures may include the presentation of comprehensible information about the necessity and kind of the intervention, mechanism of action, material risks, and consequences or alternative treatments [3, 5]. The principle of informed consent is based on the human right for self-determination and the ethical principle of autonomy [2, 6]. Informed consent is not only required by ethical aspects, but also incorporated in legal requirements. These legal requirements vary between countries [1–3]. The Council of Europe’s Convention on Human Rights and Biomedicine (chapter II, article 5), for example, declares that ‘an intervention in the health field may only be carried out after the person concerned has given free and informed consent to it. This person shall beforehand be given appropriate information as to the purpose and nature of the intervention as well as on its consequences and risk.’ For example in Germany, the role of patients has been strengthened by the Patient Rights Act in 2013 (Patientenrechtegesetz), that is incorporated into the Civil Code (para. 630a-630h BGB). Although, verbal consent is sufficient, practitioners in Germany frequently use informed consent forms to support the physician-patient-communication and to document written informed consent [5]. In contrast, the U.S. American law requires written informed consent as a prerequisite for interfering with the patient’s physical integrity [1].

This study aims at investigating the effects of evidence-based informed consent forms for total knee arthroplasty (TKA) surgery (including related anesthesia procedures) in clinical practice. Usually, informed consent for surgery does not primarily aim at proving adequate information to support an informed decision, because the decision for or against the medical intervention is usually made before hospital admission, e.g., during first consultation in primary care. However, it is not ensured that relevant information for the decision is provided in these consultations. Due to high liability risks for treatment errors, informed consent for surgery and related consent forms often focus on risk-centered information [3, 4, 7]. The way of presenting treatment risks can affect patients’ anxiety and the nocebo effect, which can be defined as ‘unpleasant or adverse outcomes triggered by the treatment context, beyond any inherent […] effects of the treatment itself’ [8–11]. Previous research shows that supporting documents (e.g., informed consent forms) used in practice are heterogeneous [12, 13] and that they are often deficient regarding the communication of risks [13].

## Objectives

The overall aim of this project is to investigate whether newly developed evidence-based informed consent forms for surgery and anesthesia (on the example of TKA) can reduce the deficits of the standardized consent forms regarding patients’ anxiety, nocebo effects, and risk perception. For this purpose, we will develop evidence-based informed consent forms and compare them with standard consent forms as used in routine care in Germany.

Specifically, we will perform the following sub-studies:
I.Qualitatively explore the information acquisition process and the decision-making processesII.Develop (including pilot testing) evidence-based informed consent forms for total knee arthroplasty and related anesthesia procedures (regional and general anesthesia)III.Conduct an interrupted time series (ITS) pilot study to test the effects of evidence-based informed consent forms in comparison with standard consent formsIV.Perform a formative process evaluation to identify barriers and facilitators to the implementation of the intervention and to analyze contextual factors and mechanisms of impact

## Logic model

The potential impact of information presented in informed consent forms on health outcomes depends on complex processes. Figure 1 depicts these complex processes and how informed consent forms may affect health outcomes.

**Fig. 1 Fig1:**
[figure not shown]
Logic model

Negative expectations are important elements of the complex processes which may produce nocebo effects [11]. Negative expectations are caused by negative stimuli, which are the results of assimilating internal and external factors through complex cognitive-emotional-processes [14]. External factors are primarily the information from informed consent forms. Other important factors might be pre-existing health literacy and other information sources. The source and content of information and the presentation of information may influence which subjective meaning is given to the information. Assimilating these external factors can evoke internal factors, in particular emotions like fear or even anxiety [14].

Via (neuro-)physiological pathways negative expectations, caused by the negative stimuli, may influence the likelihood of experiencing these expectations (e.g., headaches). This may in turn negatively affect the quality of life [15, 16].

In addition, anxiety [17] and dissatisfaction with the decision may have an immediate negative impact on quality of life.

## Methods

The development, piloting, and evaluation of evidence-based informed consent forms for TKA and related anesthesia procedures will follow the UK MRC Framework for developing and evaluating complex interventions [18]. The UK MRC Framework describes four key elements of the development and evaluation process: (1) development, (2) feasibility/piloting, (3) evaluation, and (4) implementation. This study will include the first two key elements: Sub-studies I and II will be performed for developing the intervention; sub-studies III and IV will be performed for exploring feasibility and pilot testing the intervention (see Fig. 2).

**Fig. 2 Fig2:**
[figure not shown]
Sub-studies in accordance with the UK MRC Framework

This study protocol is reported according to the *Standard Protocol Items: Recommendations for Interventional Trials (SPIRIT)* [19], where applicable.

The study—including all sub-studies—is approved by the Ethics committee of the Witten/Herdecke University (reference number 198/2020). We will receive written informed consent from all participants prior to inclusion.

## Development

We will perform sub-studies I and II to develop the intervention.

### Sub-study I: exploration of the information acquisition process and the decision-making processes

We will explore the information acquisition processes and the decision-making processes to better understand the context in which the informed consent form is embedded. The informed consent on TKA and anesthesia is the final step in the decision-making process. Our aim is to describe the whole process to understand when, how, and by whom decisions are made and what information is decisive. We will derive information needs and preferences of patients, and identify barriers and facilitators for the adequate use of evidence based informed consent forms in practice.

We will perform semi-structured interviews with patients and physicians. Patients will be asked to describe their personal course of knee osteoarthritis. For specific situations in the course, they will be asked open-ended questions with regard to the objective. For example: how do you describe the information you received? How did your decision to have the surgery come about? Physicians, for example, will be asked about the information they give patients and how they involve patients in decision making. Patients, ≥ 18 years, with decision-making capacity, considering TKA or with previous TKA in the last 6 months will be included. Physicians (orthopedics and anesthetists) obtaining informed consent in the clinic for orthopedics, trauma surgery, and sports traumatology of the Cologne-Merheim Hospital as well as referring orthopedics and primary care physicians are eligible. Physicians in the clinic will be personally addressed, and referring physicians will be invited by email and phone. If they agree to participate, they will also receive information flyer for patients. Patients will be recruited by study nurses or physicians during the office hours of the clinic or ambulant consultations. Written informed consent will be obtained. Due to the corona pandemic, we will conduct online or telephone interviews. The interviews will be audio recorded and transcribed. We will perform a qualitative content analysis to develop categories and report on commonalities and differences. The analysis will be performed in an iterative process until no new categories can be derived and data saturation is achieved [20].

In addition, written information (leaflets, decision aids, and consent forms) on TKA provided by participating physicians or received by included patients, will be collected and rated with the ensuring quality information for patients (EQIP) scale [21] regarding criteria of evidence-based health information. Descriptive analysis will be performed.

### Sub-study II: development and pilot testing of evidence-based informed consent forms

#### Development of evidence-based informed consent forms

To promote informed choices, evidence-based informed consent forms on TKA and related anesthesia procedures (regional and general anesthesia) will be developed, taking insights from sub-studies I and II into account [22–26].

The design of the evidence-based informed consent forms, will be guided by an existing guideline on how to present evidence-based health information (*guideline evidence-based health information* [27]) and nocebo research. The information will be presented in plain language. Benefits and harms of the procedures will be presented in absolute risk formats and in comparison with other interventions or placebo [28]. Verbal presentations of risks lead to overestimations of risks [29] and therefore, will not be applied exclusively. Gain and loss framing will be combined. To visualize important aspects, pictograms will be used. Information on uncertainty, missing, or low-quality evidence will be provided.

We will perform systematic reviews on the comparative effectiveness and harms of TKA and related anesthetic procedures to generate quantitative information for developing the informed consent forms. Relevant research questions for the systematic reviews will be derived from former consent forms, reviews, guidelines, patient preferences, and in cooperation with the participating practitioners. We will include systematic reviews, randomized controlled trials, and prospective cohort studies. For rare adverse events and complications, we will consider database-based studies such as medical device registries or adverse event reporting systems, in addition. The quality of evidence will be rated according to GRADE [30]. Eligibility-screening of references, data extraction, and critical appraisal will be performed by two independent reviewers.

To resume the current state of research, we will review comparative studies on written material to promote informed consent identified in previous systematic reviews on this topic [31, 32].

We will derive relevant information on benefits and risks for the knowledge test, for usage in the main study (objective III). The development will be based on previous experiences with the measurement of informed choice [33, 34].

Due to the special legal requirements for informed consent, we will prove evidence-based consent forms for satisfying legal requirements. The lawyers of our team will perform a comprehensive evaluation of case law and literature (monographs, articles, commentaries, especially on the §§ 630d, 630e BGB) on the legal aspects regarding informed consent in Germany. During this process, the legal scope that may result from more recent jurisdiction on the physician’s obligation to provide information and the requirements for evidence-based informed consent forms will be examined and compared. At the same time, the legal framework for future patient-oriented education is defined in the concept of informed consent.

#### Pilot testing

The new consent forms will be tested on comprehensibility, readability, acceptance, and emotional response. Think-aloud interviews are planned, in which participants share their thoughts while reading the consent form, followed by at least two focus group interviews with patients of the target group. The interviews will be audio recorded and transcribed. Qualitative content analyses will be performed [20]. The consent forms will be revised and tested in an iterative process until data saturation is achieved.

The knowledge questions for sub-study III will also be pilot tested. We will optimize the items and select the most appropriate for the knowledge test.

In addition, a member from the *Health Information Department* of the independent *Institute for Quality and Efficiency in Health Care* (IQWiG), clinical experts and lawyers from the respective scientific medical societies (*The German Society for Endoprosthetics* and *The German Society for Anaestesiology and Intensive Care Medicine*, *DGAI*) and the study center will review the informed consent forms.

## Feasibility/piloting

### Sub-study III: monocentric interrupted time series (ITS) pilot study

We will conduct a monocentric pilot study. This pilot study will be performed following a pragmatic trial approach to increase applicability to the German context of informed consent procedures [35]. Our primary analysis is an ITS analysis approach. Using an ITS analysis, will allow us to compare the outcome trend (level and/or slope changes) before and after the introduction of the newly developed evidence-based informed consent forms [36].

### Methods: participants, interventions, and outcomes

#### Study setting

The study will be conducted in an urban region (Cologne) at a level III hospital in Germany (Cologne-Merheim Hospital).

#### Eligibility criteria

Participants eligible for inclusion in the study:
Are scheduled for an elective total knee arthroplasty surgeryAre at least 18 years oldAre able to understand and speak GermanAre mentally competent to give consent and answer questions

Patients with revision total knee arthroplasty (rTKA) or post-traumatic arthrosis will be excluded.

Hospital staff or study nurses will check the inclusion criteria for each potentially relevant patient at consultation during the office hours of the clinic for orthopedics, trauma surgery and sports traumatology of the Cologne-Merheim Hospital.

#### Interventions

We include two groups of participants before (pre) and after (post) the introduction of the intervention. The group in the pre period (control group) will give informed consent based on standard consent forms from the Thieme-compliance publisher (https://shop.thieme-compliance.de/patientenaufklaerung/thieme/de/Artikel/Aufkl%C3%A4rungsb%C3%B6gen/c/00000), which represents routine care in the study center. The group in the post-period (intervention group) will give informed consent based on our newly developed evidence-based informed consent forms (see sub-study II). The change of the informed consent forms will be introduced at a pre-specified time-point. The informed consent procedures for surgery and for anesthesia will be performed together as far as feasible in the usual hospital workflow.

In addition, physicians performing informed consent in the post-phase will be offered a training in evidence-based decision-making to adequately implement the evidence-based informed consent forms. The training will be based on the basic curriculum for evidence-based decision-making, developed by the *German Network for Evidence-based Medicine*. A curriculum-based, blended learning training program for physicians and medical students has already been developed and pilot tested [37]. This training will be converted to an e-learning module to be independent of possible restriction due to the COVID-19 pandemic. In addition, e-learning with only short phases of virtual presence offers more flexibility. The training will also be adapted to address evidence-based decision-making on TKA. For major changes pilot testing will be considered.

#### Blinding

Standard consent forms and evidence-based informed consent forms are obviously different. Therefore, blinding of medical staff will be impossible. We will not explicitly inform participants about receiving a “different” informed consent form but only about the nature of the study. The statistical analysis will be performed blinded.

#### Outcomes and measurement instruments

We plan to measure the following patient-relevant outcomes:
Primary outcomes:Anxiety: subjective fear/anxiety of adverse events possibly caused by surgery or anesthesia
○ Measuring instrument: numeric rating scale 0–10 (validation see [38, 39]) and surgical fear questionnaire (SFQ) [40]. The SFQ comprises 8 items reflecting different aspects of surgery-related fear (e.g., anesthesia or side effects). All items are scored on a numeric rating scale 0–10. It is validated in adult patients scheduled for an elective surgery.○ Measure: meanNocebo-effect: patient reported adverse events (e.g., headache after anesthesia)
○ Measuring instrument: a questionnaire will be developed. We will use closed simple-choice questions (yes/no) to detect frequent adverse events and open-ended questions to detect other (less common) adverse events.○ Measure: proportion of patients with complications or adverse eventsSecondary outcomes:Knowledge or risk perception: questions for knowledge about benefits and risks
○ Measuring instrument: objective knowledge questions (e.g., correct risk assessment) derived in the development phase. The development will be based on previous experiences with the measure of informed choice [33, 34].○ Measure: proportion of correctly answered questionsSatisfaction with the physician-patient-communication and informed consent form
○ Measuring instrument: numeric rating scale 0–10 (validation see [41])○ Measure: meanQuality of life (QoL)
○ Measuring instrument: numeric rating scale 0–100 (validation see [42])○ Measure: meanPain and function
○ Measuring instrument: Oxford Knee Score (OKS) [43]. The OKS is a 12-item questionnaire with five scoring categories (validation see [43]).○ Measure: mean

#### Sample size

To our knowledge, no comparative studies on different informed consent forms for TKA and related anesthesia procedures in the German context exist so far. Therefore, a sufficient data basis for statistical sample size calculation is not available. With this pilot study, we aim to create the data basis for sample size calculation and detect unforeseen problems (e.g., in recruitment, processes) for a definitive trial to prove effectiveness. We calculated the sample size for this pilot study using the probability to identify unforeseen problems [44] as anticipated to provide a robust basis for a valid sample size calculation in a definitive trial.

We plan to include at least 220 participations (110 pre, 110 post) in the study. Based on findings from previous studies [10], we anticipate a dropout rate of 10% so that 198 participants can be included in the analysis. Using this sample size, unforeseen problems with a 2% probability of occurrence can be identified with a probability of 98%. We based the sample size calculation on such conservative values to increase the planning certainty of a future trial.

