This study will be performed under routine conditions. Despite focusing on only one indication, we anticipate that the basic impact tendency may be generalized to other indications and settings. If this pilot study indicates positive effects of the newly developed evidence-based informed consent forms, it is planned to perform a definitive cluster-randomized trial for a wide range of different indications. Relations to publishers of informed consent forms already exist. Thus, if this pilot study indicates positive effects of evidence-based informed consent forms, this is a good starting situation to develop further evidence-based informed consent forms in cooperation. The use of informed consent forms is widespread. Therefore—premised a definitive study shows that the improvement of patient-relevant outcomes is possible—a large-scale implementation could have an important positive impact on a population level.

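### The 98% chance of detecting a 2% problem applies only to problems that can arise in both phases; for problems specific to the new forms or the physician training it is 86–89%

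*Protocol article*

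**What the plan says.** All of the sizing is in the Sample size section of the protocol article.

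- Enrolment: "We plan to include at least 220 participations (110 pre, 110 post) in the study".
- Attrition: "we anticipate a dropout rate of 10% so that 198 participants can be included in the analysis".
- Result: "Using this sample size, unforeseen problems with a 2% probability of occurrence can be identified with a probability of 98" per cent.
- Purpose: to "detect unforeseen problems (e.g., in recruitment, processes) for a definitive trial to prove effectiveness". The detection rule is also expected "to provide a robust basis for a valid sample size calculation in a definitive trial".

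The section describes these inputs as conservative. It does not say that the detection probability refers to the two phases taken together.

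Other sections show who is exposed to what. Under Interventions, Recruitment and Participant timeline, patients in the first 12 months receive the standard forms and patients in the second 12 months receive the new ones. The training in evidence-based decision-making is offered to physicians who obtain consent in the post-phase. The pilot runs in one hospital (Sub-study III, Study setting). Should it indicate benefit, the Discussion says that "it is planned to perform a definitive cluster-randomized trial for a wide range of different indications".

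**The concern.** The plan has no power calculation, and the Statistical model section rules out significance testing. The detection probability is therefore the only quantitative support for the sample size. A reader will take it to cover any problem the pilot is meant to reveal, including problems with the intervention itself. The Methods section places sub-study III under feasibility and pilot testing of the intervention, so such problems are central to its purpose.

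Pre-phase patients never see the new forms, and their physicians have not been offered the training. They cannot contribute to finding a problem with either. For that class of problem, about half of the 198 patients carry no information, and pooling is the optimistic choice rather than the conservative one. At stake is how confidently the team may conclude, after an uneventful post-phase, that no 2% problem with the new forms exists.

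A second, smaller issue is the statement that the sample gives a robust basis for sizing the definitive trial. One hospital can supply some of the quantities needed, but not all of them if that trial randomizes hospitals.

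**Working it through.** **Inputs.** From Sample size: 220 enrolled, 110 per phase, 10% dropout, 198 analysed, problem probability 0.02, stated detection probability 98%. The number analysed per phase is not stated. With equal dropout in the two phases it is 110 × 0.9 = 99.

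**Formula.** The probability of seeing a problem at least once in n independent patients, each with probability p, is 1 − (1 − p)^n.

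**Reproducing the plan's figures.**
- 220 × 0.9 = 198, as stated.
- 1 − 0.98^198 = 0.9817, or 98.2%, which matches the stated 98%.

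**Same formula, post-phase only, p = 0.02.**

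| Patients counted | n | Detected | Missed |
|---|---|---|---|
| Both phases, analysed | 198 | 98.2% | 1.8% |
| Post-phase, analysed (equal dropout) | 99 | 86.5% | 13.5% |
| Post-phase, all enrolled | 110 | 89.2% | 10.8% |

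As a cross-check, a problem with probability 2% in one phase and 0% in the other averages 1% over both. With n = 198, 1 − 0.99^198 = 86.3%, close to the 86.5% above.

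**Which problems the post-phase finds with 98% probability.** Solve 1 − (1 − p)^n = 0.98, so p = 1 − 0.02^(1/n):
- n = 99: p = 0.0387, about 3.9%.
- n = 110: p = 0.0349, about 3.5%.

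**What 98% at p = 0.02 would take in the post-phase alone.** n = ln 0.02 / ln 0.98 = 193.6, so 194 analysed. At 10% dropout, 194 / 0.9 = 215.6, so 216 enrolled in that phase. This shows the size of the gap and is not a recommendation to enlarge the pilot.

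**Basis for the definitive trial.** With one hospital there are 1 − 1 = 0 degrees of freedom for between-hospital variance, so an ICC across hospitals cannot be estimated. The document gives no ICC and no cluster size, so the following is an assumed range for illustration only. With design effect 1 + (m − 1) × ICC and ICC from 0.01 to 0.10, the result is 1.19 to 2.90 for m = 20 patients per hospital and 1.49 to 5.90 for m = 50.

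**The case against.** The strongest reply is that nothing has been miscalculated. That is right: both the dropout step and the 98% reproduce. A reader might infer an arithmetic error from the lower post-phase figures, but the documents do not support that. The issue is the scope of the claim.

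Next, the section's own examples are recruitment and processes. Screening, enrolment, interviews and follow-up are the same in both phases, and for these n = 198 is the proper denominator. This stands, and 98% should be kept for them. But the examples are introduced as examples, and the sentence giving 98% has no restriction.

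A reader might also infer that problems with the forms would largely escape notice. The documents do not support this either. Sub-study II tests the forms in think-aloud interviews and focus groups, with expert and legal review, before the post-phase. Sub-study IV documents each consent process and interviews physicians and 20% of intervention patients. These safeguards lessen the consequence, but they do not make 98% the correct probability for form-specific problems in sub-study III.

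The figure of 99 is the less favourable choice. Enrolment is a minimum, and a problem may be seen in a patient who later drops out. Hence the range of 86–89%; its upper end is still well below 98%.

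On the definitive trial, the cluster-randomized design appears only in the Discussion and is conditional on positive results. The Sample size section never promises an ICC, and its source can reasonably be left to that trial's own protocol. It would go too far to say that the pilot cannot inform the definitive sample size. The point is only that the statement should be limited to what one centre can provide. Limitations admits restricted external validity from a single hospital, but does not draw this consequence.

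**Conclusion.** The concern holds as a matter of scope. The 98% is correct for problems that occur with 2% probability in both phases. For problems specific to the new forms or the training, the design gives about 86% (99 analysed) or 89% (110 enrolled). The chance of missing such a problem is thus 10.8–13.5%, against 1.8% pooled.

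This assumes independent patients with a constant problem probability and, for the 99, equal dropout by phase. It also assumes the problem cannot arise before the change of forms. That is clear for the forms and the training. It is less clear for joint surgical and anaesthetic consent, which the Interventions section does not plainly confine to the post-phase, so that component is left out of the claim.

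The point about the definitive trial is narrow. It applies if hospitals are the clusters, which the article does not state, although the remark in Limitations about the expense of a cluster design points that way. No estimate or analysis in the pilot changes, and the findings do not show that the pilot is too small for its purpose.

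**What to change.** Keep 220 participants and revise two statements in the Sample size section.

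1. Give the detection probability by type of problem: 98% for 2% problems that can occur in both phases (198 analysed), and 86–89% for 2% problems specific to the intervention (99 analysed to 110 enrolled in the post-phase). Add that 98% is reached in the post-phase for problems of about 3.9% or more with 99 patients, or 3.5% or more with 110. A cross-reference to sub-studies II and IV, as further means of finding form-specific problems, would put the lower figure in context.
2. Limit the claim about the definitive trial to what one hospital can estimate: within-hospital standard deviations, event rates, recruitment and retention. Note that if the trial is cluster-randomized by hospital, the ICC will be taken from external sources over a stated range.

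The cost is a few sentences and a less favourable figure for one class of problem. No additional patients, data or analyses are needed.
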